#### **7.8. Direct Access to Source Data/Documents**

Upon request, the Investigator shall supply the Sponsor with any required background data from the study documentation or clinic records. This is particularly important when CRFs are illegible or when errors in data transcription are suspected. In case of special problems and/or governmental queries or requests for audit inspections, it is also necessary to have access to the complete study records, provided that patient confidentiality is protected.

FHI will be responsible for the clinical monitoring of the study. FHI clinical research assistants (CRAs) will visit the participating center to review the research records for accuracy, completeness and legibility.

The Investigator will make study documents (for example, consent forms, treatment forms, CRFs) and pertinent hospital/clinic or clinic records readily available for inspection by the study monitor for confirmation of the study data.

**7.9. Investigator Information****7.9.1. Protocol approval and signature**

After reading the protocol, the Investigator will sign two protocol signature pages and return one of the signed pages to the Sponsor.

**7.9.2. Study agreements**

The principal Investigator and all study staff must comply with all the terms, conditions and obligations of the study agreement for this study.

**7.9.3. Publication policy**

All information concerning pyronaridine artesunate and the Sponsor's operations, such as the Sponsor patent applications, formulas, manufacturing processes, basic scientific data, or formulation information, supplied by the Sponsor and not previously published is considered confidential information.

The information developed during the conduct of this clinical study is also considered confidential and will be used by the Sponsor in connection with the development of pyronaridine artesunate. This information may be disclosed as deemed necessary by the Sponsor. To allow for the use of the information derived from this clinical study and to ensure complete and thorough analysis, the Investigator is obligated to provide the Sponsor with complete test results and all data developed in this study.

This confidential information shall remain the sole property of the Sponsor, shall not be disclosed to others without the written consent of the Sponsor, and shall not be used except in the performance of this study.

The Sponsor encourages publication of study results. However no study data shall be disclosed prior to the final analysis of the data. Should an Investigator wish to publish results from this study, a copy of the manuscript must be provided to the Sponsor at least 30 days before the date of submission to the intended publisher.

**7.10 Financing and Insurance**

This study is to be conducted in accordance with the standards stipulated in this protocol and Clinical Trial Agreement. The Sponsor, Shin Poong Pharm Co Ltd. and Medicines for Malaria Venture, will indemnify the Principal Investigator, co-Investigators, and other relevant parties from all and any claims arising from this study with the exception of claims resulting from their negligence, malpractice or

violation of the protocol.

In the event that it can be demonstrated that a patient suffers any significant deterioration in health or well-being or any harmful susceptibility or toxicity as a direct result of their participation in this study then Shin Poong Pharm Co Ltd and Medicines for Malaria Venture will agree to abide by International Guidelines and local regulations with regards to the compensation payable to the patient. The amount of compensation will be calculated by reference to the cost of best standard care provided by the local health system for similar injuries at the time when such injury occurred.

#### **7.11. Study Timetable and Termination**

The planned start date for this study is Q4 2006. It is anticipated that accrual will take up to approximately 5 months per site and the proposed patient completion date is estimated as Q2 2007.

## 8. DATA MANAGEMENT

The Data Management will be performed by an independent contract research organisation (CRO).

The top, white, no carbon required (NCR) copy of each CRF will be sent to the data management group for the study. The middle copy of the CRF will be retained by the monitoring CRA and the bottom copy will be retained by the Investigator. On receipt at the CRO, the CRFs will be logged into an electronic tracking system. The data will be entered onto a database using blind double data entry. Where the data violate validation checks, queries will be generated via Data Clarification Forms (DCFs). These forms may be generated as three-part NCR paper that is colour-coded to match the CRF, or as electronic files. DCFs will be sent to the monitoring CRA for resolution by the Investigator. On receipt of the original resolution at the CRO (a copy retained by the CRA and the Investigator), the database will be edited appropriately. Information on the status of each data clarification form (DCF) will be maintained in an electronic tracking system within the database. All edits made to the database on resolution of the DCFs will be electronically audit-trailed and 100% quality control (QC) checked.

Medications will be coded using the WHO-drug dictionary. Medical conditions and AEs will be coded the MedDRA dictionary.

When data entry has been completed and all outstanding queries have been resolved for a CRF, it will be eligible for QC checking. A  $\sqrt{n} + 1$  sample of patients will be selected for QC checks and 100% of these data will be audited. In addition, 100% of demography, AEs and withdrawal data will be checked for all patients. The highest acceptable error rate for QC is 0.5%. A higher error rate will prompt a review of a further sample of  $\sqrt{n} + 1\%$  of patients. If the error rate remains above 0.5%, a 100% QC check of all data will be conducted. All errors discovered will be corrected on the database and the corrections will be audit-trailed and will undergo a QC check.

Before database lock, a further  $\sqrt{n} + 1\%$  sample of patients will be selected for quality assurance (QA) checks. The highest acceptable error rate for QA is 0.5%. A higher error rate will prompt the same actions as for QC. All errors discovered on the database will be corrected and the corrections will be audit-trailed. On satisfactory completion of the QC and QA checks, the database will be locked.

## 9. STATISTICAL METHODS

The statistical methods for this study, summarised below, will be described in a detailed statistical analysis plan (SAP) which will be finalised and approved before database lock. Any deviations from the planned analysis as described below or in the SAP will be justified and recorded in the final study report.

### 9.1. General Considerations

Data will be summarised as follows: Continuous variables by descriptive statistics (number of patients [n], mean, standard deviation [SD], minimum, median, maximum); categorical data by absolute and relative frequencies (n and %) or contingency tables.

Unless indicated otherwise, summary statistics will be reported for observed data only. Missing data will not be imputed. If a baseline value is missing, no change from baseline will be calculated. Baseline is defined as the last observation prior to the first administration of study medication.

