### 3. METHODS AND INVESTIGATIONAL PLAN

#### 3.1. Study Design Overview

The study is designed as a multicentre, randomized, double-blind, double-dummy, parallel group, comparative trial.

Patients will be randomized to receive either oral pyronaridine artesunate (180:60 mg tablets), plus chloroquine-placebo or oral chloroquine (155 mg tablets), plus pyronaridine artesunate-placebo, once a day for 3 consecutive days. Patients will be followed for 42 days after the first study drug administration, the primary efficacy endpoint occurring at Day 14.

For patients who complete the study up to Day 28 and who have normal G-6-PD-activity, a 14-day course of primaquine (15 mg/day) shall be administered starting on Day 28, after all required assessments have been performed, to complete their radical cure. Patients who are deficient in G-6-PD and who complete the study up to Day 28 will be treated as per country policy. For all patients, a final safety assessment will be performed on Day 42.

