### **3.3. Patient Discontinuation or Protocol Violation**

A patient may withdraw consent at any time, without prejudice for further follow up or treatment by the study site.

A patient may be discontinued prematurely from the study if the Investigator decides that a patient should be withdrawn for safety reasons, due to an adverse event of such a nature or intensity (including abnormal laboratory finding), where study drug withdrawal or withdrawal from the study is advisable. Information concerning any adverse event and symptomatic treatment given must be recorded on the case record form (CRF). If the adverse event is serious, the Investigator must notify the Sponsor or its designee immediately and the reporting procedures described in the safety section must be followed. Definitions and reporting requirements for adverse events are provided in section 5.2.4.

Self or third party administration of antimalarial (or antibiotics with antimalarial activity) treatment other than for treatment failure will be classified as a protocol violation. A list of Forbidden Medication is provided in Attachment 5.

In the case of a patient vomiting the first dose (Day 0) within 0 to 30 minutes of study drug administration, a repeat full dose will be given. If patient vomits the study drug on either the second (Day1) or third day (Day 2) of dosing or if the patient vomits a re-administered dose on Day 0, they will not be re-dosed but will be withdrawn from the study. A patient who is withdrawn due to vomiting should receive rescue medication, after having completed end of study (Day 28) assessments.

A patient who terminates participation after any study drug administration for any reason will be considered as having discontinued from the study and will have

end of study (Day 28) procedures performed. The reason for discontinuation will be recorded on the CRF. If a patient is discontinued for an adverse event, the Investigator will continue to follow the patient until resolution or until no further medically relevant information can be expected.

Every effort must be made to schedule a follow-up visit for patients who fail to return to the study site after administration of the study drug. Women who inadvertently become pregnant during the study must be followed to full term and the outcome of the birth fully documented on a specific form provided by Sponsor.

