#### **4.5. Drug Administration**

Study drug will be administered to patients by a qualified member of the study site who has been designated by the Investigator. All parties will be blind to treatment assignment and will not be informed of treatment allocation unless the blind needs

to be broken for a medical emergency. Sealed envelopes with treatment allocation will be available at each site to be opened only in case of emergencies. Patient's weight at screening should be used to calculate the number of tablets to be administered.

Study drug will be given to each patient with up to 240 ml (full glass) water. All tablets must be swallowed. Patients will take the medication in an upright position (seated or standing). The patient may be given food prior to drug administration. Initial drug administration day is designated Day 0. A dispensing record detailing the number of tablets administered for each patient, as well as the date and time, will be maintained. Exact time of dose administration will be recorded in the CRF. Dosing on the two subsequent days will occur no less than 10 hours after the previous dosing. Exact time of daily dose administration will be recorded in the CRF.

In the case of a patient vomiting the first dose (Day 0) within 0 to 30 minutes of study drug administration, a repeat full dose will be given. If patient vomits the study drug on either the second (Day 1) or third day (Day 2) of dosing or if the patient vomits a re-administered dose on Day 0, they will not be re-dosed and will be withdrawn from the study. A patient who is withdrawn due to vomiting must be given rescue medication.

Unused medication will remain in a locked cabinet in the pharmacy until full accountability has been performed by the Sponsor or its designee and instructions given for their return to Shin Poong.

Patients with normal G-6-PD activity (as at screening) and who complete the study up to Day 28 will be given a 14-day course of primaquine (15 mg/day) in an open-label manner starting on Day 28, after all required assessments have been completed. For women of childbearing potential, a negative pregnancy test should be demonstrated before starting primaquine treatment. Primaquine treatment should not be administered to pregnant women.

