#### Intent-To-Treat Population (ITT)

The Intent-to-Treat (ITT) population will consist of all randomised patients who have received any amount of study medication. Patients will be analysed as randomized.

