#### Efficacy Evaluable (EE) Population

The efficacy evaluable (EE) population will include those patients in the ITT population meeting pre-defined criteria as follows:

1. Having completed a full course of study medication and having known efficacy endpoints.
2. No missed dose due to vomiting, as recorded on the 'study medication administration page' of the CRF, except at Day 0 where a patient may vomit after the first drug administration and have a repeat full dose. In this case, the repeated dose should not be vomited.

3. No concomitant medication (except paracetamol) which may interfere with the treatment outcome, up to Day 14. The list of forbidden medication is given in Attachment 5. A medical review will be performed to confirm the exclusion of a patient from the EE population.
  4. No concomitant disease, such as Tuberculosis, HIV, severe URTI, gastrointestinal disease, etc..., which may interfere with the clear classification of the treatment outcome. A medical review of the experienced diseases will be performed to define the list of patients excluded from the EE population.
  5. No major protocol violation. The list of all protocol violations will be assessed with regards to their impact (major/minor) prior to database lock.
- The list of patients excluded from the EE population will be reviewed and approved prior to study unblinding and database lock.

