#### **Secondary Efficacy Analyses:**

The primary efficacy analysis performed on Day 14 will be repeated for the proportion of patients with cure on Day 21 and 28, using the efficacy evaluable population.

In addition, the analysis performed using the EE population will be repeated using the ITT population.

The parasite clearance time and fever clearance time will be analysed using Kaplan-Meier estimates. The median and quartiles clearance time will be presented together with the corresponding 95% confidence intervals. The mean will also be calculated. The survival curves will be presented. The log rank test will be used to compare the parasite clearance time and fever clearance time between the two treatment groups. Patients who do not have documented parasite or fever clearance will be censored. Censoring time will be greater than the highest observed clearance time.

The proportion of patients who have parasite clearance and the proportion of patients who have fever clearance will be presented at Day 1, Day 2 and Day 3. The associated exact 95% confidence interval will also be calculated.

The number of parasites will be summarized using standard descriptive statistics, as well as geometric mean and its associated 95% confidence interval using an analysis of variance model on  $\log_{10}$  transformed parasites counts with treatment and site as factors. The mean parasite count at each scheduled timepoint will be presented graphically.

All secondary efficacy analyses will be performed both on the EE and ITT populations.

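### As written, the ITT repeat of the cure analysis most naturally drops early withdrawals, and can score some patients given another antimalarial as cured, so it is a weak check on the EE result

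*Protocol*

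**What the plan says.** **Missing data.** Section 9.1 limits summary statistics to observed data, with room for stated exceptions, and then says: "Missing data will not be imputed". Nothing in 9.2 or 9.5 indicates otherwise for cure.

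**Populations.** Section 9.2: "The Intent-to-Treat (ITT) population will consist of all randomised patients who have received any amount of study medication". The primary analysis uses the EE set, whose first criterion is "Having completed a full course of study medication and having known efficacy endpoints"; a dose missed through vomiting also excludes a patient. In 9.5.2, under the secondary analyses, "the analysis performed using the EE population will be repeated using the ITT population".

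**Withdrawal.** Sections 3.3 and 4.5 withdraw a patient who vomits the Day 1 or Day 2 dose, or a repeated Day 0 dose. In 3.3, "A patient who terminates participation after any study drug administration for any reason will be considered as having discontinued from the study", and the Day 28 end-of-study procedures are then done. Section 4.5 adds: "A patient who is withdrawn due to vomiting must be given rescue medication". Neither section mentions a Day 14 smear after withdrawal. Section 3.1, however, says "For all patients, a final safety assessment will be performed on Day 42", and the Synopsis promises the same final assessment to all patients.

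**Cure.** The Definitions, section 9.5.1 and Attachment 3 require a negative smear on the day and no earlier failure criterion. The failure criteria are hospitalisation for deterioration with parasitaemia, parasitaemia with fever from Day 3, and any parasitaemia from Day 7. Withdrawal, rescue and other antimalarials are not among them. An antimalarial taken for a reason other than treatment failure is a protocol violation (3.3; Synopsis, Concomitant Treatment).

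**The concern.** In a non-inferiority trial, an analysis of completers can hide a difference, because patients who could not tolerate or finish treatment are removed. The ITT repeat is meant to show whether the conclusion survives when they are put back. If the same patients also leave the ITT cure rate for lack of a Day 14 smear, ITT adds little beyond protocol deviators with a known outcome, and agreement between the two analyses says little. The same applies to the Day 21 and Day 28 analyses.

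A second, distinct problem affects other patients. A person in ITT who received a non-study antimalarial and is smear-negative on Day 14 meets the written definition of cure, so the effect of another drug is credited to the study drug. The two problems cannot affect the same patient at the same timepoint: one needs an absent smear, the other a negative one.

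**Working it through.** **Inputs.** From 9.4: 90% cure in both arms, margin 10 points, two-sided 95% interval, 205 evaluable per arm, 10% drop-out, 228 randomised per arm. The drop-out is 456 - 410 = 46 patients. The split of those 46 between arms, and equal 90% cure among observed patients, are my assumptions.

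**The plan's own figures.** Without continuity correction, n = 2 x 0.90 x 0.10 x (1.960 + 1.282)^2 / 0.10^2 = 189.1, so 190 per arm. With continuity correction it is 209, close to the stated 205. Power at 205 per arm is 92.1% without and 89.4% with the correction. Allowing for drop-out, 410 / 0.9 = 455.6, so 456. The sample size reproduces and is not in question.

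**Two ways of counting a missing outcome.** With m lost in an arm:
- Observed case: cure = 0.90 x (228 - m) / (228 - m) = 90%, whatever m is.
- Missing = not cured: cure = 0.90 x (228 - m) / 228.
- Lower limit = d - 1.96 x sqrt(p1(1 - p1)/n1 + p2(1 - p2)/n2), where d is pyronaridine artesunate (PA) minus chloroquine (CQ).

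For 27 v 19 lost:
- Observed case: d = 0, SE = sqrt(0.09/201 + 0.09/209) = 0.0296, lower limit -5.8 points.
- Missing = not cured: 180.9/228 = 79.3% and 188.1/228 = 82.5%, d = -3.2, SE = 0.0368, lower limit -10.4 points.

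| Lost PA / CQ | Observed-case lower limit | Missing = not cured: difference | Lower limit |
|---|---|---|---|
| 23 / 23 | -5.8 | 0.0 | -7.2 |
| 25 / 21 | -5.8 | -1.6 | -8.8 |
| 27 / 19 | -5.8 | -3.2 | -10.4 |
| 30 / 16 | -5.8 | -5.5 | -12.7 |

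The observed-case result does not respond to the split at all.

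**Another antimalarial before Day 14.** Assume k PA patients are rescued without meeting a failure criterion and are smear-negative on Day 14, with 90% cure otherwise, no other losses and 228 per arm. The lower limits are:

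| k | Counted cured | Excluded | Counted not cured |
|---|---|---|---|
| 2 | -5.4 | -5.5 | -6.4 |
| 10 | -5.0 | -5.6 | -9.9 |

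**Who is in that group.** Three kinds of patient:
- Protocol violators, who remain in ITT and whom no section withdraws.
- Patients withdrawn for vomiting and rescued who nevertheless return on Day 14.
- Patients with parasitaemia but no fever on Day 3. The Day 3 note in section 6 treats remaining significant parasitaemia as failure leading to withdrawal and rescue, but in 9.5.1 parasitaemia without fever or hospitalisation counts only from Day 7.

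**The case against.** The strongest reply is that an observed-case ITT is an inference. The no-imputation sentence is a general rule that allows exceptions, no section says an ITT patient without a smear leaves the denominator, and ITT contains every dosed patient. Because cure requires a negative Day 14 smear, a patient without one is simply not shown to be cured and could stay in the denominator with nothing imputed. The EE requirement for known endpoints could be taken to imply that ITT keeps unknown ones. This stands in part: the protocol permits that reading, and an SAP that is not shown may adopt it. It does not make it the natural one, since the observed-data rule is explicit and 9.5.2 simply repeats the EE analysis.

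A reader might also infer more than the documents support:
- **That withdrawn patients are not followed.** Section 3.3 requires end-of-study procedures, follow-up of adverse events that led to discontinuation, and efforts to schedule a visit for patients who fail to return. Only a Day 14 smear after withdrawal is unspecified.
- **That intolerance disappears from the report.** Reasons for withdrawal (5.2), population counts by arm (9.3) and adverse events leading to discontinuation (9.5.2) are all reported. What is missing is their effect on the cure comparison.
- **That rescued patients in general count as cured.** Anyone rescued after meeting a failure criterion stays a failure.
- **That the new combination will lose more patients.** Phase I adverse events were predominantly gastrointestinal, but no subject stopped because of them, and the protocol lists gastrointestinal effects for chloroquine too.

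Finally, counting missing as not cured is not conservative in every case. With equal 10% loss it multiplies a true difference by 0.9, so -10 points becomes -9. Hence both analyses are needed.

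**Conclusion.** The point holds in a limited form. On its most natural reading, the protocol's ITT cure analysis loses the same early withdrawals as EE and gives little protection against a non-inferiority conclusion that depends on their removal. Separately, the cure definition lets a small, specific group treated with another antimalarial count as study-drug cures in ITT.

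The size depends on an imbalance that the documents neither state nor predict. Within the planned loss of 46, a split of 27 v 19 (11.8% v 8.3% of 228) is enough to carry the lower limit from -5.8 to -10.4 points; 25 v 21 is not, and balanced loss leaves the difference at 0. The claim that ITT is certainly observed-case, or that any withdrawn or rescued patient is miscounted, goes beyond the text. Because ITT is a secondary analysis and the remedy is wording, this should be corrected before unblinding but does not undermine the design.

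**What to change.** In 9.5.2, state for the ITT analyses at Days 14, 21 and 28:
1. Every ITT patient stays in the denominator, apart from the cases in point 3.
2. A patient with no outcome at the timepoint, or given a non-study antimalarial before it, counts as not cured. Observed-case ITT is kept as a sensitivity analysis.
3. Patients with P. falciparum infection after clearance of P. vivax are handled separately, for example excluded or censored, with a sensitivity analysis, because 9.5.1 and Attachment 3 say they are not P. vivax failures. Without this, point 2 would count them as such.

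Two sets of passages must also be reconciled: section 3.3 with section 3.1 and the Synopsis on which visits a discontinued patient attends up to Day 42, and the Day 3 note in section 6 with the failure criteria in 9.5.1.

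The cost is mainly wording; any visits that the first reconciliation adds would be extra. The reported ITT cure rate falls: with balanced 10% loss it is 0.9 x 0.90 = 81%. Power for that analysis is then Phi(0.10 / sqrt(2 x 0.81 x 0.19 / 228) - 1.96) = 77.7%, against the 90% planned for EE. The protocol states no ITT power, so this should be disclosed in advance.
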